# 1. Overview

## **Title of study**

EPOCH (Evaluating a Point-Of-Care device in Heart Healthcare)

## **Study period**

Expected duration 3-6 months (dependent on practices' rate of risk assessment).

## **Objectives**

To evaluate the impact of POC testing for lipids (TC/HDL) and diabetes (HbA1c) on the frequency of completed cardiovascular disease (CVD) risk assessments in the eligible population in primary care practice. The primary aim of this study is to determine whether POC testing for lipids (TC/HDL) and diabetes (HbA1c) is at least as effective as the control (laboratory) on the frequency of completed cardiovascular disease (CVD) risk assessments in the eligible population at 12 months in primary care practice.

## **Study design and methodology**

Pragmatic, prospective, open, blinded endpoint, cluster randomised controlled trial with non-inferiority design. Twenty general practices: 10 randomised to receive the POC device, 10 continue with laboratory testing for lipids and diabetes.

## **Study population**

Patients aged 35-79 years who are eligible for CVD risk assessment.

## **Number of subjects**

Minimum of 1000 risk assessments (approximately 50 per practice).

## **Main criteria for inclusion**

Adults aged 35-79 years who are eligible for CVD risk assessment based on age, sex, ethnicity, previous CVD risk assessment).

## **Exclusion criteria**

Ineligible for CVD risk assessment, or have a previous completed CVD risk assessment within the recommended time. Aged < 35 years or ≥ 80 years.

## **POC group**

Cobas b 101: finger prick point-of-care testing medical device for total cholesterol/ high-density lipoprotein (TC/HDL) and haemoglobin type A1c (HbA1c).

## **Laboratory (control) group**

Usual laboratory testing for TC/HDL and HbA1c.

## **Criteria for evaluation**

### *Primary outcome*

Completed CVD risk assessments at end of study.

### *Secondary outcomes*

Incomplete ("parked") CVD risk assessments at end of study.

Completed CVD risk assessment by age, sex, Māori/non Māori, diabetes, smoking status, deprivation quintile, practice location (urban/rural), practice size, previous CVD risk score.  
 Average duration of CVD risk assessment.  
 Cost analysis.  
 Acceptability, feasibility and practice impact of POC testing for TC/HDL and HbA1c in general practice.

### **Statistical methods**

#### *Study power*

Assuming an intraclass correlation coefficient of 0.025, a two sided 5% significance, a sample size of 10 practices with an average of 50 patients each, in each of the two arms, will confer 90% power to detect a difference in completed CVD risk assessments of 10-15% between the POC practices and laboratory practices.

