## 7. Statistical Considerations

### 7.1 Sample size

The study will involve a two-arm parallel cluster randomised controlled trial (CRCT) design with 20 practices (10 practices per arm). The primary outcome is whether the eligible patients have had a completed CVD risk assessment during the study. Preliminary analyses indicated that at least 70% of the enrolled populations within Manaia and Te Tai Tokerau PHOs have had a completed CVD risk assessment since 2006. Many of these people will be due for repeat CVD risk assessment. Significant delays to the conduct of this trial have occurred both prior to commencement and having to halt the trial due to manufacturing problems of the HbA1c discs. During this time practices have accelerated their CVD risk assessments in order to meet the national target (by July 2014 that 90% of the eligible population have had a CVD risk assessment in the previous 5 years.) As at April 2014, the two PHOs have screened approximately 80% of their eligible enrolled populations over the last five years. Therefore this trial now needs to adopt **a priori a non-inferiority hypothesis**.

Our previous sample size calculations May 2013, were as follows; We assumed a primary event rate of 70% in the laboratory group and a 10-15% increase to 85% in the POC group. This figure is based on a study set in community pharmacies where POC testing for cholesterol risk management led to a 10% increase. Taking into account an intraclass correlation coefficient of 0.025 as suggested by Elley et al (2005) from three New Zealand CRCTs; a 5% two-sided level of significant test and study power of 90%, we estimate a minimum sample size of 1000 risk assessments is needed (on average 50 patients per practice).

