Our updated sample size calculations are based on analyses estimating the number of eligible people who are eligible for first risk assessment and those that will require a follow-up CVD risk assessment (for example those over 15% CVD risk, and people with diabetes are recommended for annual screening). Within a 12 month period (Aug 2012-2013) it appeared that about 30% of the eligible population had a CVD risk assessment. We assume a primary event rate of 30% in the laboratory group and a 10% increase to 40% in the POC group. This figure is based on a study set in community pharmacies where POC testing for cholesterol risk management led to a 10% increase. The non-inferiority margin is set at 5%. Taking into account an intraclass correlation coefficient of 0.025 as suggested by Elley et al (2005) from three New Zealand CRCTs; a 0.025 one-sided level of significance and study power of 90%, we estimate a minimum sample size of 940 risk assessments (470 in each group) and 10 practices per group is needed assuming an average of 50 patients per practice. Therefore, the sample size is similar to the previous power calculations.

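### The Overview claims 90% power for a 10-15% difference, but the planned design gives about 61-69% at 10 points, and the claim rests on the superseded superiority calculation

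*Protocol*

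**What the plan says.** Under Study power, the Overview (section 1) sets out a superiority calculation. It opens "Assuming an intraclass correlation coefficient of 0.025, a two sided 5% significance", takes "a sample size of 10 practices with an average of 50 patients each, in each of the two arms", and concludes that this "will confer 90% power to detect a difference in completed CVD risk assessments of 10-15% between the POC practices and laboratory practices". It gives no control rate and no margin.

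Under Study design and methodology, the same Overview describes a "cluster randomised controlled trial with non-inferiority design".

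Section 7.1 gives two calculations. The first is introduced with "Our previous sample size calculations May 2013, were as follows" and reads "We assumed a primary event rate of 70% in the laboratory group and a 10-15% increase to 85% in the POC group", with a two-sided 5% test and 90% power. Section 7.1 explains that screening coverage rose during the delays and that the trial therefore now needs a non-inferiority hypothesis. The updated calculation assumes 30% in the laboratory group and 40% in the point-of-care (POC) group, a one-sided 0.025 level and 90% power, and arrives at 940 assessments (470 per group). On the margin it says: "The non-inferiority margin is set at 5"%.

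Section 7.2.2 keeps superiority as a follow-on test, done only if non-inferiority is shown.

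**The concern.** There are two faults in one sentence.

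First, the power figure does not follow from the inputs stated beside it. Clustering at an intraclass correlation of 0.025 with 50 patients per practice more than halves the effective sample, and what remains is too small for 90% power at the lower end of the stated range.

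Second, the sentence keeps the May 2013 superiority basis as if it were current. Someone who reads only the Overview would learn neither the margin nor the control rate. Nor would they learn that the trial's 90% power for non-inferiority depends on POC testing being truly 10 points better.

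This matters because a superiority test is still planned. A reader who trusts the Overview would treat a non-significant superiority result as strong evidence against a 10-point gain. At the assumed rates, the trial would miss such a gain in 31% to 39% of repetitions.

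**Working it through.** **Inputs.** From the Overview, Study power: intraclass correlation 0.025, two-sided 5%, 10 practices of 50 per arm (500 per arm). From section 7.1, because the Overview gives no control rate: 30% (current calculation) and 70% (previous calculation).

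**Effective sample size.** Design effect = 1 + (50 − 1) × 0.025 = 2.225. Effective n per arm = 500 / 2.225 = 224.7.

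**Power for superiority.** SE = √{[p₁(1 − p₁) + p₂(1 − p₂)] / 224.7}; power = Φ(difference / SE − 1.96).

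| Control v POC | Difference | SE | diff/SE − 1.96 | Power |
|---|---|---|---|---|
| 30% v 40% | 10 points | √(0.45/224.7) = 0.0447 | 0.27 | 60.8% |
| 70% v 80% | 10 points | √(0.37/224.7) = 0.0406 | 0.50 | 69.3% |
| 30% v 45% | 15 points | √(0.4575/224.7) = 0.0451 | 1.36 | 91.4% |
| 70% v 85% | 15 points | √(0.3375/224.7) = 0.0388 | 1.91 | 97.2% |

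A pooled variance changes these little (60.4%, 68.8%, 91.0% and 97.0%). A t reference with 18 degrees of freedom (20 practices − 2) lowers the 10-point figures to 56% and 64%.

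**Smallest difference with 90% power** (same formula, solved for the difference): 14.6 points from 30% and 12.8 points from 70%; 14.7 and 12.9 with pooled variance.

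**Sample size needed for 90% power at 10 points** (pooled variance): 477 × 2.225 ≈ 1,062 per arm for 30% v 40%, and 392 × 2.225 ≈ 873 per arm for 70% v 80%, against 500 planned.

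**Attempts to recover the stated 90% at 10 points.**
- A one-sided 5% test gives 72% (30% v 40%) or 79% (70% v 80%).
- Reading 10% as a relative increase gives 10% (from 30%) or 39% (from 70%).
- Ignoring clustering gives 91% or 96%, but the sentence itself states an intraclass correlation.

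**The section 7.1 non-inferiority figure.** With 30% v 40% and a 5-point margin, the distance from the margin is 10 + 5 = 15 points. The individually randomised size is (1.96 + 1.2816)² × 0.45 / 0.15² = 210.1, rounded up to 211 per arm. Multiplying by 2.225 gives 469.5, so 470 per arm and 940 in total, as stated. Power is 90.1% with 470 per arm and 91.8% with 500 (88.7% with 500 per arm and 18 degrees of freedom).

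**The case against.** The best defence is that the Overview names no control rate, so the range could mean the smallest detectable difference over a span of unspecified rates, and not 90% power at every point in it. By the same formula that difference is 14.6 points at a 30% control rate, 15.1 at 40%, 14.9 at 50%, 14.2 at 60%, 12.8 at 70% and 10.7 at 80%, which is close to the stated range. The previous calculation is also amply powered at the end it spells out: 70% v 85% gives 97%.

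This reading does not save the sentence. Section 7.1 shows where the range comes from: it is an assumed increase from a single 70% rate, not a span over control rates. The current assumed effect is exactly 10 points. Even an 80% control rate, which section 7.1 mentions only as five-year coverage, gives just 85% power at 10 points.

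Three parts of the defence do stand. The shortfall is at the lower end of the range, not throughout it. Superiority has been dropped only as the hypothesis that sets the sample size; it remains as a conditional test, judged by a confidence interval that readers will see. And the fault lies in a summary, while section 7.1 is correct on its own assumptions, so neither the sample size nor the primary test is affected.

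**Conclusion.** The concern holds. At 10 points the design has 61% power (30% control rate) or 69% (70% control rate), not 90%; with 18 degrees of freedom the figures are 56% and 64%. At 15 points the claim is met, at 91% and 97%. The sentence also states the previous superiority basis in an Overview that calls the trial non-inferiority.

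These figures assume absolute differences, equal practices of 50 patients, the stated intraclass correlation, and control rates borrowed from section 7.1 because the Overview gives none. The planned 1,000 assessments meet the section 7.1 requirement of 940 on that section's own assumptions, so the error is confined to what the Overview says the trial can detect.

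**What to change.** Replace the Study power text in the Overview with the current basis from section 7.1: 30% completion in the laboratory group, 40% assumed in the POC group, non-inferiority limit −5 points, one-sided 0.025, intraclass correlation 0.025, and 10 practices per arm averaging 50 patients. State that power is about 90% with 470 per arm and 92% with 500, and that this depends on the assumed 10-point POC advantage.

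Add one sentence on the follow-on superiority test: with 500 per arm and a 30% control rate, power is about 61% for a 10-point gain and 91% for a 15-point gain (normal approximation). That sentence goes beyond removing the contradiction, but without it readers have no correct figure in place of the 90%.

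The cost is a text amendment. Sample size, conduct and analysis do not change; the stated superiority power becomes less favourable.

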#### *Statistical analysis*

Intention-to-treat analysis of the primary outcome. Generalized estimating equations (GEE) or random effects mixed models will be used. Statistical process control charts (run charts) will demonstrate monthly CVD risk assessment.

### **Funding**

Roche Diagnostics International Limited.  
 Roche Diagnostics NZ Limited.

## 2. Study Plan Schematic

[figure not shown]

Abbreviations: GP = general practitioner, CVD = cardiovascular disease

### 3. Background

#### 3.1 CVD risk assessment

Cardiovascular diseases (CVD) are readily preventable long term conditions that contribute to major ethnic and socioeconomic disparities in New Zealand. Interventions are available that could halve cardiovascular events (such as myocardial infarction and stroke) but the magnitude of treatment benefit is directly proportional to the magnitude of pre-treatment absolute CVD risk.

New Zealand CVD management guidelines recommend identifying people at high risk of developing CVD using a modified version of the Framingham risk prediction equation. Screening is recommended for all men over 45 years, all women over 55 years and 10 years earlier for people who are of Māori (indigenous New Zealanders), Pacific or South Asian ethnic groups, or people with known CVD risk factors. The intensity of management is then tailored according to a patient's five-year CVD risk.

Recently, new CVD and diabetes health targets for healthcare organizations have been introduced by the New Zealand Ministry of Health (MoH).a From January 2012 the Ministry will measure the number of completed CVD risk assessments for all eligible persons within the last five years (including diabetes checks). Data will be sourced from the Primary Health Organisation (PHO) performance programme. To assist District Health Boards (DHBs) in achieving the target of 90%, interim targets have been set over the next two years. The first is 60% by 1 July 2012, then 75% by 1 July 2013, and full achievement of the national target of 90% by 1 July 2014. PHOs and their member general practitioners (GPs) are well-informed of these targets via a number of mechanisms. These include PHO performance being annually benchmarked against others, PHOs receiving incentive payments (albeit modest) according to CVD risk assessment performance and planned PHO activities encouraging practice compliance such as CME/CNE and other practice interventions (such as visiting facilitators).

Up to 2011, we estimated that only about one third of the eligible population from the combined Northland and Auckland regions had been risk assessed and this was mainly via opportunistic screening. However, in the last 18 months there has been a marked acceleration of CVD risk assessment activity with some PHOs reporting 60%-70% screening of their eligible population.

The ultimate aim of the MoH is to shift the measure of quality from the proportion who have had a CVD risk assessment to the proportion who have received effective management (e.g. prescription uptake and medication adherence). Targets incorporating effective management are likely to be developed post 2014. Recommended CVD risk management is currently not being systematically offered to patients based on their level of CVD risk. New Zealand studies indicate that both over- and under-use of cardiovascular interventions is common in both primary and secondary prevention. A recent audit of patients with established CVD found that while most were receiving aspirin, 30% were not taking a statin and a further 30% were not prescribed any blood pressure (BP) lowering drug. An audit of patients without a history of CVD visiting their general practitioners in 2000 showed that there was little evidence that CVD risk management was being targeted to those at highest risk.

a <http://www.health.govt.nz/new-zealand-health-system/health-targets/2011-12-health-targets/health-targets-better-diabetes-and-cardiovascular-services-more-heart-and-diabetes-checks>

### 3.2 PREDICT CVD software tool

All GPs in Northland have access to the PREDICT CVD risk assessment and management tool. PREDICT is a web-based decision support system used since 2002 in New Zealand in a variety of settings - general practices, community outreach screening, workplaces (occupational health assessments) and in secondary care (Coronary Care Units and Medical Outpatient Clinics). Integrated with primary care patient management systems (PMS), PREDICT provides clinicians and patients with tailored evidence-based CVD risk prediction and management support. As of the last quarter of 2012, 360,000 New Zealanders in primary and secondary care have had a PREDICT CVD assessment. In addition, risk communication software, Your Heart Forecast, is integrated with the PREDICT platform. PREDICT and associated research has been supported through Health Research Council and National Heart Foundation funding.

The PREDICT CVD risk assessment and management program has been fully integrated with the electronic patient medical record that is used at the time of consultation. When a primary care provider wishes to do a CVD risk assessment they simply open the CVD risk assessment window. Items such as the New Zealand National Health Index (NHI number) unique patient identifier, ethnicity, laboratory results (if available), blood pressure recordings, prior history of CVD or diabetes, will be automatically populated from the electronic patient record into the appropriate fields of the template.

When a clinician uses PREDICT for CVD risk assessment and/or management, they submit patient data to the PREDICT server and within seconds receive a CVD risk calculation for the patient as well as guideline recommendations tailored to an individual's CVD risk profile. A copy of this transaction is saved both on the electronic patient medical record and in the PREDICT server. Once a risk assessment is conducted the provider can go directly to the Heart Forecast via PREDICT to begin discussing with the patient what their CVD risk is, their burden of modifiable disease and suggest appropriate evidence-based management.

### 3.3 Assessment of cholesterol and diabetes

As part of a CVD risk assessment, the New Zealand guidelines recommend blood lipid testing and use of the ratio of total cholesterol to high density lipoprotein (TC/HDL, fasting or non-fasting) in the risk calculation. In 2009, screening for diabetes was also recommended as part of the risk assessment using either fasting glucose or haemoglobin type A1c (HbA1c, fasting or non-fasting).

Currently, if the lipid and diabetes values are not known at the visit, the GP or practice nurse must order a blood test (via a laboratory referral form). Transmission from the screen to the PREDICT server will not occur unless all the data fields are filled in. If screening blood tests are not available the assessment can be "parked" and saved until all data is subsequently available. Ideally then a risk assessment would be completed with the patient on a second visit. It is not known what proportion of risk assessments remain incomplete due to the laboratory testing step and necessity for two consultations.

### 3.4 Point-of-care testing for cholesterol and HbA1c

A new point-of-care (POC) device (Cobas b 101 developed by Roche Diagnostics) that can perform both TC/HDL and HbA1c tests has recently become available on the New Zealand and global markets. It is estimated that a thirty minute consultation could provide a completed CVD risk assessment (see figure below and Appendix 3). This includes 15 minutes to undertake the finger prick sampling and provide the test results. The Cobas b 101 practitioner to complete the risk assessment and provide tailored advice in the one consultation.

# CVD Risk Assessment

## *cobas b 101 local study proposal*

[figure not shown][figure not shown][figure not shown]

### cobas b 101 – The HbA1c & Lipid Monitoring System Two Tests from One Finger Prick – Possible Through Heparin Coating

[figure not shown][figure not shown]

## 5. Study Objectives

Primary study objective:

To evaluate the impact of POC testing for lipids (TC/HDL) and diabetes (HbA1c) on the frequency of completed CVD risk assessments in the eligible population. The primary aim of this study is to determine whether POC testing for lipids (TC/HDL) and diabetes (HbA1c) is at least as effective as the control (laboratory) on the frequency of completed cardiovascular disease (CVD) risk assessments in the eligible population at 12 months in primary care practice.

Secondary study objective(s):

1. To evaluate the impact of POC testing for TC/HDL and HbA1c on the frequency of incomplete ("parked") CVD risk assessments in the eligible population.
2. To evaluate the impact of POC testing for TC/HDL and HbA1c on CVD risk assessments in the eligible population by age, sex, deprivation quintile, for Māori and non Māori, diabetes, smoking status, and previous CVD risk score.
3. To evaluate the impact of POC testing for TC/HDL and HbA1c on the average duration of CVD risk assessment.
4. To evaluate whether the impact of POC testing is the same in urban areas (e.g. Whangarei City) as in rural areas and in large and small GP practices.
5. To conduct a cost analysis of POC testing compared with laboratory testing.
6. To evaluate the acceptability, feasibility and practice impact of POC testing for TC/HDL and HbA1c in general practice.

## 6. Study Design

This is a pragmatic, prospective, open, blinded endpoint, cluster randomised controlled non-inferiority trial in primary care.

The study setting is the patients enrolled in GP practices within the Northland region of New Zealand that belong to either Manaia Health Primary Healthcare Organization (PHO) or Te Tai Tokerau PHO. Manaia Health has 24 practices and Te Tai Tokerau has 15. A cluster randomised controlled trial is proposed within twenty of these general practices who use PREDICT and agree to participate in the study.

The eligible population is comprised of patients enrolled in these practices who are aged between 35-79 years, who as determined by their GP, meet age, sex and ethnicity guideline criteria for CVD risk assessment (Table1) and do not have a previous recorded CVD risk assessment or if they have had a previous CVD risk assessment are overdue for their next check (Table 2). All CVD risk assessment data will be automatically captured within the PREDICT server before, during, and after the study as part of usual clinical practice.

The unit of randomisation will be the practice and data collection will be at the individual patient level. The study involves random allocation of the practices to either the POC group (Cobas b 101) or laboratory (control) group. A cluster RCT design was necessary because the cobas b 101 device will be provided to the practice as a cluster level intervention.

